### Outcome parameters

The outcome parameters are tumour free margins (and number of re-excisions), resection specimen volume, cosmetic outcome, quality of life, cost effectiveness also participating physicians will score the difficulty of the procedures. Patients will be asked to fill in questionnaires on pain during the procedure, quality of life and the cosmetic outcome. A specific burden questionnaire, aimed at evaluating the burden of the cosmetic result, is developed. Such an instrument is currently not available. To further assess the net impact in terms of Health Related Quality of Life (HRQoL) also the EQ5D and the EQVAS will be obtained at T = 0, 6, 12 and 26 weeks after the initial diagnostic work-up.

The outcome of the study can be divided in 3 groups of outcome; negative outcomes, outcomes open to discussion and positive outcomes.

Less tumour free margins in the ROLL group are considered negative outcomes, also more tumour free margins in combination with a larger resection volume is a negative outcome and equal tumour free resection margins combined with larger resection specimens are considered negative. Secondly outcomes open to discussion are more tumour free margins in combination with an equal resection volume and equal resection margins in combination with smaller resection specimens in the ROLL group. Finally positive outcomes are more tumour free resection margins in combination with smaller resection specimens and equal tumour free margins in combination with smaller resection specimens. These data will be based on pathology reports. All surgical specimens will be analysed by one dedicated reference pathologist ([name]).

The overall outcome will be cost-effectiveness in terms of incremental costs per quality adjusted life years gained with a 6 month time horizon. We hypothesize that the short-term burden will result in an overall superior result after ROLL.

When indeed our expectations are evidenced, than a situation of dominance may occur, i.e., costs may be saved while at the same time clinical effects are optimal after ROLL.

Should the results indicate that overall the WGL procedure leads to better clinical outcome a cost-effectiveness analysis is foreseen using bootstrapping to assess the uncertainty with regard to the balance between costs and effects. All analyses will be limited to a half year time horizon. Accordingly, discounting of costs or effects is not applicable.

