### Economic evaluation

The goal of the economic evaluation is to assess the balance between costs and effects of ROLL versus WGL. The principal underlying assumption is that once tumour free margins are obtained the prognosis will be similar.

Therefore, long term analyses will not be necessary. In fact ignoring the possible difference in burden associated with WGL as compared to ROLL a cost-minimization would suffice. This is the initial approach, i.e., comparing actual costs incurred with both strategies up until 6 months after the first operation. Costs estimates will be based on the actual costs of both procedures. This includes the costs of operation rooms, hospital stay, ultrasound/stereotactic imaging, wire placement, gamma probe use and if necessary, costs associated with complications and re-operations.

To assess the impact of the psychological burden of prolonged uncertainty regarding curative excision and the psychological burden associated with re-operation, dedicated questionnaires are developed.

Finally, there is a possibility that after ROLL, on average, a larger part of the breast is excised leading to less satisfactory cosmetic results. This is evaluated by interviewing the patients on their appreciation of the shape and appearance of their breast.

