### Statistical analysis

The difference in radicality of the resected specimen in both groups will be calculated in a confidence interval (CI) of 95%.

The volume of the specimens is presented in mm^3 ^and the maximum diameter in mm. The approach for the cost-analysis is comparing actual costs incurred with both strategies up until 6 months after the first operation. Costs estimates will be based on the actual costs of both procedures. This includes the costs of operation rooms, hospital stay, ultrasound/stereotactic imaging, wire placement, gamma probe use and if necessary, costs associated with complications and re-operations.

The degree of difficulty of radiological and surgical procedure will be expressed on a 1–10 scale (1 being extremely easy and 10 extremely difficult). The average score for both procedures will be calculated. Patient discomfort of the radiological procedure is expressed on 1–10 scale to (1 being not painful and 10 being very painful).

The success rate of the sentinel node procedure is presented in a percentage of successfully detected and found sentinel nodes.

The weight and size of the surgical specimens as well as the degree of difficulty of the surgical and radiological procedures and patients discomfort in both groups will be analyzed using the students T test.

The cost-effectiveness analysis will be done using the multivariate analysis. If the baseline characteristics differ after randomization, i.e. there is a lack of balance in the confounding factors, this will be corrected using the multivariate analysis.

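### Incremental cost per QALY is a poor choice of overall outcome: it cannot be read if ROLL is dominant, and it is unstable if the 6-month QALY difference is near zero

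*Protocol article*

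**What the plan says.** All places are in the protocol article.

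- **Outcome parameters** sets the summary measure: "The overall outcome will be cost-effectiveness in terms of incremental costs per quality adjusted life years gained with a 6 month time horizon".
- The same section states the expected direction: "We hypothesize that the short-term burden will result in an overall superior result after ROLL". It then describes the result if expectations are met: "than a situation of dominance may occur, i.e., costs may be saved while at the same time clinical effects are optimal after ROLL".
- An uncertainty method is attached to the opposite case: "Should the results indicate that overall the WGL procedure leads to better clinical outcome a cost-effectiveness analysis is foreseen using bootstrapping". What is to be bootstrapped there is the balance of costs against effects.
- **Economic evaluation** gives the premise: "The principal underlying assumption is that once tumour free margins are obtained the prognosis will be similar". It concludes that, burden aside, comparing costs would be enough, and makes cost-minimization the initial approach.
- **Statistical analysis** adds: "The cost-effectiveness analysis will be done using the multivariate analysis".
- **Sample size** names tumour free margins as the primary endpoint, with 158 patients per arm.
- **Discussion** expects 15% fewer re-operations (600 of about 4,000 patients a year) at about EUR 7,000 each.

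**The concern.** A cost-per-QALY ratio can be interpreted when both differences have the same sign, so that one arm costs more and does more. The plan hopes for a different case, in which ROLL costs less and does more. There the ratio is negative. A negative ratio does not show which arm dominates, and a larger absolute value does not mean a better result.

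The plan's premise adds a second difficulty. If prognosis is similar, only short-term burden can separate the arms on QALYs over 6 months. The denominator may then be small relative to its sampling error. The estimated ratio would swing between large negative and large positive values, and a dominance verdict based on point estimates alone would appear or vanish with the sign of that denominator.

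At stake is how far the stated overall outcome can support the conclusion drawn in the Discussion, where cost-effectiveness is to be weighed before nationwide adoption.

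**Working it through.** **The plan's own cost figure.** 0.15 × 4,000 = 600 re-operations avoided, and 600 × EUR 7,000 = EUR 4,200,000, as the Discussion states. Per patient this is 0.15 × EUR 7,000 = EUR 1,050.

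**Reading the ratio under dominance.** Ratio = cost difference / QALY difference (ROLL minus WGL). The QALY values are illustrative; no SD is needed.

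| Cost difference (EUR) | QALY difference | Ratio (EUR per QALY) | Meaning |
|---|---|---|---|
| -1,050 | +0.01 | -105,000 | ROLL dominant |
| +1,050 | -0.01 | -105,000 | ROLL dominated |
| -1,050 | +0.001 | -1,050,000 | ROLL dominant, tiny gain |
| -1,050 | +0.02 | -52,500 | ROLL dominant, larger gain |

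The first two rows are opposite findings with the same number. The last two show that, for a fixed saving, the better result has the smaller absolute ratio.

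**Plausible size of the QALY difference.** The documents give no utility loss, so these are assumptions, and they count avoided re-operations only:
- loss of 0.1 for 6 weeks: 0.15 × 0.1 × 6/52 = 0.0017 QALY
- loss of 0.2 for 12 weeks: 0.15 × 0.2 × 12/52 = 0.0069 QALY

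**Chance of a wrong-signed difference.** SE = SD × √(2/158) = SD × 0.1125, and P(estimate < 0) = Φ(-true gain / SE). The QALY SDs are assumed.

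| QALY SD | SE | Gain 0.003 | Gain 0.005 | Gain 0.01 | Gain 0.02 |
|---|---|---|---|---|---|
| 0.06 | 0.0068 | 33% | 23% | 7% | 0.2% |
| 0.08 | 0.0090 | 37% | 29% | 13% | 1% |
| 0.10 | 0.0113 | 39% | 33% | 19% | 4% |

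**Spread of the ratio.** Simulation with 158 per arm, true saving EUR 1,050, QALY SD 0.08, cost SD EUR 3,000 (assumed), and costs and QALYs uncorrelated. Central 95% of the estimated ratio:
- gain 0.005: about EUR -1.6 million to +1.6 million per QALY
- gain 0.01: about EUR -1.1 million to +0.9 million
- gain 0.02: about EUR -270,000 to -12,000

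The SE of the cost difference is 3,000 × 0.1125 = EUR 338. The estimated cost difference therefore favours ROLL in Φ(1,050/338) = 99.9% of the same trials. The instability comes from the denominator alone.

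**Net monetary benefit on the same inputs.** INMB = threshold × QALY difference - cost difference. At an assumed EUR 20,000 per QALY and a gain of 0.005: 20,000 × 0.005 + 1,050 = EUR 1,150. SE = √(338² + (20,000 × 0.0090)²) = √(338² + 180²) = EUR 383, so the 95% half-width is about EUR 750. With a QALY difference of exactly zero, INMB is EUR 1,050 with the same half-width, whereas the ratio is undefined.

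**The case against.** The strongest reply is that the plan does not rely on the bare quotient. It names dominance as a situation of its own, so a reader need not suppose that a negative ratio would be printed. Cost per QALY gained is also the customary label for a cost-utility analysis. Cost-minimization comes first and does not use the ratio. The primary endpoint and sample size are untouched. An article may leave thresholds and acceptability curves to a fuller plan, so their absence alone is no defect.

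Most of this stands, and it rules out several stronger readings that a reader might infer:

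- *The cost question would go unanswered.* Not supported: the initial comparison of actual costs answers it without the ratio.
- *Multivariate analysis cannot be used.* Not supported: patient-level costs and QALYs can be regressed jointly, and the text does not say that the ratio is the regression outcome.
- *The planned bootstrap would itself break down.* Not supported: its stated target is the balance of costs and effects, which fits resampling of cost-effect pairs.
- *The ratio is bound to be unstable.* Not supported: the documents give no QALY SD, cost SD or utility loss. Wire discomfort, prolonged uncertainty and cosmetic burden could make the gain larger than re-operations alone suggest.

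The reply does not remove two things. Dominance judged from point estimates depends on the sign of the QALY difference, and the article ties its bootstrap to the case that it does not expect. Cost-minimization sets aside the burden that the plan hopes will favour ROLL.

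**Conclusion.** The point holds as a weakness in the chosen summary measure. That the ratio is uninterpretable under dominance follows from its definition and needs no assumption. Its instability is conditional. With a QALY SD of 0.06 to 0.10 and a true gain of 0.003, the difference has the wrong sign in about 33% to 39% of trials; at a gain of 0.02 this falls to 4% or less, and the ratio is fairly stable though still negative. All these SDs and gains are assumptions. In the expected case the plan attaches no bootstrap to the verdict and names only an unspecified multivariate analysis. The consequence is limited to the cost-utility result. The change is worth making but does not bear on the trial's primary conclusion.

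**What to change.** In Outcome parameters:

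1. Report the cost difference and the QALY difference separately, each with a 95% CI.
2. Express cost-effectiveness as incremental net monetary benefit over a stated range of thresholds, with a CI and an acceptability curve.
3. Obtain these from a joint bootstrap of patient-level costs and QALYs, or from patient-level regression, whichever arm does better clinically.
4. Quote a ratio only when both differences have the same sign.

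In Statistical analysis, say that the multivariate analysis is applied to patient-level net benefit, or to costs and QALYs jointly.

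The change needs wording only. It uses the cost and EQ5D data already planned and leaves the sample size alone. The one real cost is that a threshold range must be named and defended in advance.

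### Bootstrapping of the cost-effect balance is foreseen only for the case in which WGL does better clinically; no uncertainty method is stated for other results, and three sections describe different economic analyses

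*Protocol article*

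**What the plan says.** All places are in the Methods/Design part of the protocol article.

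- *Outcome parameters*, the target: "The overall outcome will be cost-effectiveness in terms of incremental costs per quality adjusted life years gained with a 6 month time horizon". No condition is attached.
- *Outcome parameters*, if the trial's expectations are met: "than a situation of dominance may occur, i.e., costs may be saved while at the same time clinical effects are optimal after ROLL". No method for the uncertainty of that finding follows.
- *Outcome parameters*, if the result goes the other way: "Should the results indicate that overall the WGL procedure leads to better clinical outcome a cost-effectiveness analysis is foreseen using bootstrapping". The stated purpose is "to assess the uncertainty with regard to the balance between costs and effects". Bootstrapping is mentioned nowhere else in the article.
- *Economic evaluation*, the goal: "The goal of the economic evaluation is to assess the balance between costs and effects of ROLL versus WGL". The starting point, however, is cost-minimisation: "In fact ignoring the possible difference in burden associated with WGL as compared to ROLL a cost-minimization would suffice", which the section calls its initial approach.
- *Statistical analysis*: "The cost-effectiveness analysis will be done using the multivariate analysis". This carries no condition. It mentions neither the bootstrap nor an interval for the cost-effectiveness result.

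**The concern.** An economic comparison estimates two differences, in cost and in QALYs, and both carry sampling error whichever arm comes out ahead. The article recognises this when WGL does better and is silent otherwise. The stated analysis therefore depends on the result. WGL's advantage would be examined for joint uncertainty, while the plan puts no such requirement on an advantage for the technique that the trial expects to win.

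The Discussion says that the trial aims to prove ROLL superior on cost-effectiveness, among other things, and links cost-effectiveness to nationwide adoption. A dominance claim reported without its uncertainty would bear directly on that aim. With three differing descriptions, the analyst could also choose among them after seeing the data.

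**Working it through.** **1. The plan's own figures.** The economic evaluation states no figure that can be reproduced: no cost variance, QALY variance or correlation is given. The sample size (158 per arm, 15-point difference, 80% power, p < 0.05) is context only. The WGL rate behind it is not stated. With two-sided testing, 155 to 161 per arm corresponds to an assumed WGL rate of 56% to 59% without continuity correction, and 155 to 160 to a rate of 62% to 64% with it. So 158 is attainable.

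**2. The sections side by side.**

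| Clinical result | Outcome parameters | Economic evaluation | Statistical analysis |
|---|---|---|---|
| ROLL better | dominance may occur; no uncertainty method | cost-minimisation first | multivariate analysis; no interval stated |
| Equal | nothing specific to the economic analysis | cost-minimisation first | same |
| WGL better | cost-effectiveness analysis with bootstrap | cost-minimisation first | same |

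Only one cell names a method for joint uncertainty.

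**3. How often that case would arise.** Better clinical outcome is not defined for this purpose, so tumour free margins serve as a proxy. Let p be the WGL rate (assumed 60% to 80%), d the true ROLL advantage, and n = 158 per arm.

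SE = √[p(1−p)/158 + (p+d)(1−p−d)/158]; P(WGL looks better) = Φ(−d/SE).

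Example with p = 0.60 and d = 0.15: SE = √(0.24/158 + 0.1875/158) = 0.0520; Φ(−2.88) = 0.0020.

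| True ROLL advantage | P(WGL looks better) | P(WGL significantly better) = Φ(−d/SE − 1.96) |
|---|---|---|
| 15 points | 0.2% or less | practically 0 |
| 5 points | 12% to 18% | 0.2% or less |
| none | 50% | 2.5% |

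At p = 0.56, the lowest rate compatible with step 1, SE = √(0.2464/158 + 0.2059/158) = 0.0535 and Φ(−2.80) = 0.25%, so the picture does not change.

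**4. Apparent dominance under no true difference (illustration only).** Let r be the correlation between the estimated cost and QALY differences, both centred on zero and jointly normal.

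P(ROLL looks cheaper and better) = 1/4 − arcsin(r)/(2π).

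- r = 0: 25%
- r = −0.5: 1/4 + 1/12 = 33%
- r = +0.5: 1/4 − 1/12 = 17%

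The values of r are assumptions. A negative r is plausible because re-operation adds both cost and burden. The formula uses no trial input and gives WGL the same chance of looking dominant. It shows only that apparent dominance needs a statement of uncertainty.

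**5. Cost-minimisation and burden.** *Economic evaluation* reaches cost-minimisation by setting aside a possible difference in burden. *Outcome parameters* hypothesises that short-term burden makes ROLL superior overall and collects EQ5D at 0, 6, 12 and 26 weeks. The initial approach thus leaves out an effect that the QALY outcome is meant to capture.

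**The case against.** The best defence is that the article does plan a cost-effectiveness analysis unconditionally: the overall outcome has no condition, and neither has the multivariate analysis. That stands. A reader might infer that bootstrapping is excluded, or that no uncertainty analysis at all takes place, when ROLL looks better. The text supports neither. Bootstrapping is named for one case and not ruled out for others, and the multivariate analysis might yield intervals. What can be said is that none is stated.

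A reader might also infer that dominance will be read off point estimates. No such rule is in the article; it says only that dominance may occur if expectations are borne out.

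Nor does the hypothesised 15-point margin difference contradict cost-minimisation. *Economic evaluation* assumes similar prognosis once margins are free and counts re-operations as cost, so the margin difference enters through cost. The burden point is milder than a contradiction: the section openly names what it ignores, calls cost-minimisation an initial step and adds questionnaires. It remains a tension with the burden hypothesis.

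Finally, this is a condensed article. Resampling details, interval methods and graphical displays may sit in a fuller plan, and their absence is no fault. But the direction-dependent condition and the disagreement between sections are in the printed text, so this defence does not reach them.

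**Conclusion.** The point holds in this form: the one named method for uncertainty in the cost-effect balance is attached to the case in which WGL is clinically better, none is stated for the other results, and the three sections differ on whether the cost-effectiveness analysis is unconditional, conditional or preceded by cost-minimisation.

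On the trial's own hypothesis, the case with a stated bootstrap would arise in about 0.2% of trials or fewer. This rests on margins as a proxy, assumed WGL rates of 60% to 80% and a normal approximation. The 17% to 33% range for chance dominance is illustrative and should not be read as this trial's error rate or as evidence of bias towards ROLL.

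The change should be made. It does not touch the primary endpoint, the sample size or data collection.

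**What to change.** State one economic analysis that applies whatever the clinical result:

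- Estimate incremental cost and incremental QALY over 6 months by randomised arm.
- Obtain their joint uncertainty by bootstrapping patients' cost-QALY pairs.
- Report any claim of dominance, for either arm, with its bootstrap probability.
- Keep cost-minimisation as a secondary analysis, and say that it leaves out the burden difference.
- Say what the multivariate analysis contributes, for example covariate adjustment of the two differences.
- Reword *Outcome parameters*, *Economic evaluation* and *Statistical analysis* to match, and remove the condition on WGL doing better.

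The cost is a change of wording and a modest amount of extra analysis on data already planned. Recruitment, treatment and data collection stay as they are.

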### Sample size

Sample size is calculated based on the primary endpoint: tumour free margins. Based on currently available literature we assume a difference in tumour free margins of 15% in favor of the ROLL procedure [8-14]. With a statistical power of 80% to detect this 15% improvement as significant (p < 0.05), we will require 158 patients in the control (WGL) group and 158 in the ROLL group.

Assuming a weight of 50 gr in the WGL group and a difference of 10 gr in the ROLL group [15] and a standard deviation of 3 gr, α = 0.05 and β = 0.80, the groups are sufficient to show a significant reduction in weight.

### Economic evaluation

The goal of the economic evaluation is to assess the balance between costs and effects of ROLL versus WGL. The principal underlying assumption is that once tumour free margins are obtained the prognosis will be similar.

Therefore, long term analyses will not be necessary. In fact ignoring the possible difference in burden associated with WGL as compared to ROLL a cost-minimization would suffice. This is the initial approach, i.e., comparing actual costs incurred with both strategies up until 6 months after the first operation. Costs estimates will be based on the actual costs of both procedures. This includes the costs of operation rooms, hospital stay, ultrasound/stereotactic imaging, wire placement, gamma probe use and if necessary, costs associated with complications and re-operations.

To assess the impact of the psychological burden of prolonged uncertainty regarding curative excision and the psychological burden associated with re-operation, dedicated questionnaires are developed.

Finally, there is a possibility that after ROLL, on average, a larger part of the breast is excised leading to less satisfactory cosmetic results. This is evaluated by interviewing the patients on their appreciation of the shape and appearance of their breast.

### Statistical analysis

The difference in radicality of the resected specimen in both groups will be calculated in a confidence interval (CI) of 95%.

The volume of the specimens is presented in mm^3 ^and the maximum diameter in mm. The approach for the cost-analysis is comparing actual costs incurred with both strategies up until 6 months after the first operation. Costs estimates will be based on the actual costs of both procedures. This includes the costs of operation rooms, hospital stay, ultrasound/stereotactic imaging, wire placement, gamma probe use and if necessary, costs associated with complications and re-operations.

The degree of difficulty of radiological and surgical procedure will be expressed on a 1–10 scale (1 being extremely easy and 10 extremely difficult). The average score for both procedures will be calculated. Patient discomfort of the radiological procedure is expressed on 1–10 scale to (1 being not painful and 10 being very painful).

The success rate of the sentinel node procedure is presented in a percentage of successfully detected and found sentinel nodes.

The weight and size of the surgical specimens as well as the degree of difficulty of the surgical and radiological procedures and patients discomfort in both groups will be analyzed using the students T test.

The cost-effectiveness analysis will be done using the multivariate analysis. If the baseline characteristics differ after randomization, i.e. there is a lack of balance in the confounding factors, this will be corrected using the multivariate analysis.

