### Subjects

Three hundred and sixteen patients will be recruited in 2 years in a University Medical Center and medium sized to large hospitals in the Netherlands.

All patients will have confirmed occult breast cancer (core needle biopsy proven) and need to be treated with a lumpectomy and sentinel node biopsy. Written informed consent will be obtained from all patients. This study has been approved by the ethical board of the university medical center Utrecht.

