### Randomization

Randomization is stratified for hospital. In each hospital, randomization within strata is blocked with a fixed block size. Randomization is performed by an independent trial center. If a patient meets the inclusion criteria and has provided informed consent, the physician contacts the trial center by phone. The trial center will perform the randomization of the patients.

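### Randomisation is stratified by hospital but no stated analysis uses hospital, so the fixed t tests are mildly conservative and forgo a little power

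*Protocol article*

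**What the plan says.** All references are to the Protocol article.

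- **Randomization:** "Randomization is stratified for hospital", and "In each hospital, randomization within strata is blocked with a fixed block size". The block size is not given.
- **Subjects:** patients come from a "University Medical Center and medium sized to large hospitals in the Netherlands". The number of hospitals is not given.
- **Sample size:** "Sample size is calculated based on the primary endpoint: tumour free margins", and "we assume a difference in tumour free margins of 15% in favor of the ROLL procedure". The target is 158 patients per arm at 80% power and p < 0.05. No control rate is stated.
- **Statistical analysis, primary endpoint:** "The difference in radicality of the resected specimen in both groups will be calculated in a confidence interval (CI) of 95" per cent. No interval method or test is named, and stratification is neither required nor excluded.
- **Statistical analysis, continuous outcomes:** specimen weight and size, difficulty of the surgical and radiological procedures, and "patients discomfort in both groups will be analyzed using the students T test".
- **Statistical analysis, adjustment:** a multivariate correction applies if baseline characteristics turn out to differ between the arms. Hospital is not mentioned.

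**The concern.** Blocked randomisation within hospital gives nearly equal numbers per arm in each hospital. Differences between hospitals then largely cancel out of the treatment contrast, whose true sampling error comes from variation within hospitals. A pooled two-sample t test does not know this: it estimates its standard error from total variance, between-hospital part included. The standard error is then too large for the design.

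The adjustment rule does not repair this. It waits for an imbalance, and hospital is the one factor the design keeps balanced. Read literally, the plan would adjust for chance differences and leave out the factor it randomised by.

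What is at stake is precision. Specimen size, discomfort and especially the physicians' 1–10 difficulty ratings could plausibly vary by hospital, although the article gives no data on this.

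**Working it through.** **1. The plan's own sample size.** No control rate is stated, so 158 per arm cannot be derived from the stated inputs alone. With a two-sided 5% test, 80% power and a 15-point difference, the usual two-proportion formula gives 159 per arm for 57% vs 72% and 157 for 58% vs 73%. With continuity correction, 63% vs 78% gives 157. Control rates near 57–63% therefore fit the stated number.

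**2. t-tested outcomes, closed form.** Let ρ be the share of total variance lying between hospitals (the ICC), with balanced arms in each hospital.

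- True variance of the difference: 2σ²(1−ρ)/n
- Variance used by the t test: about 2σ²/n
- Ratio of standard errors: 1/√(1−ρ)
- Approximate type I error: 2Φ(−1.96/√(1−ρ))

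The standard error ratio is 1.026 at ρ = 0.05, 1.054 at 0.10 and 1.118 at 0.20. The corresponding type I error is 4.4%, 3.9% and 2.8%.

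**3. t-tested outcomes, simulation.** Assumed: 6 hospitals of 52 patients, 8,000 runs, and a true difference of 0.316 SD (about 80% power without hospital effects).

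| ICC | Type I error, t test | Power, t test | Power, arm + hospital | Forgone (points) |
|---|---|---|---|---|
| 0.05 | 4.5% | 81.2% | 82.3% | 1.1 |
| 0.10 | 4.1% | 80.9% | 83.4% | 2.5 |
| 0.20 | 3.4% | 83.1% | 87.5% | 4.4 |

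**4. Primary endpoint, if the interval is unstratified.** Assumed: 316 patients, 6 hospitals, 60% vs 75%, and normal hospital effects on the logit scale; 20,000 runs. Type I error was simulated at 74% in both arms.

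| Logit SD | Type I error, crude | Power, crude | Power, stratified | Forgone (points) |
|---|---|---|---|---|
| 0.3 | 5.1% | 82.3% | 82.4% | 0.1 |
| 0.5 | 4.7% | 83.0% | 83.7% | 0.7 |
| 0.75 | 4.1% | 83.1% | 85.0% | 1.9 |
| 1.0 | 3.9% | 83.9% | 87.5% | 3.6 |

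Crude interval coverage with no true difference was 94.9% to 96.1%. The mean standard error was 0.0516 crude vs 0.0507 stratified at SD 0.5 (ratio 1.02), and 0.0511 vs 0.0476 at SD 1.0 (ratio 1.07).

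**5. Control rate nearer the one that fits 158.** At about 57.5% vs 72.5% with logit SD 0.8, a separate simulation of 40,000 trials gave 81.4% crude and 85.3% stratified. This is not like for like, because type I error was 3.95% crude and 5.5% stratified. A 5.5% rate corresponds to a critical value of about 1.92, and 85.3% power to z = 1.05. Holding the stratified test to 5% gives Φ(1.92 + 1.05 − 1.96) = Φ(1.01), about 84%. The gap is then nearer 3 points.

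**6. Specimen weight on the plan's own figures.** With a 10 g difference, SD 3 g and 158 per arm, the standard error is 3√(2/158) = 0.338 g, so z = 29.6. Inflating the standard error by 1.118 leaves z = 26.5, so nothing changes.

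**The case against.** The strongest objection is that the primary-endpoint sentence names no method. A Mantel-Haenszel risk difference with its interval would satisfy it, and a condensed article may leave the interval method and stratification factors to an analysis plan that is not shown. This stands: a reader might infer a crude primary analysis, but the article does not state one. It does not reach the t test, which is named, or the imbalance-triggered adjustment rule, which is stated.

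A second objection is that the error is on the safe side. This also stands. A reader might infer that the intervals are invalid, but they are only somewhat too wide, and type I error stays at or below about 5%.

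Third, a reader might infer that the trial falls short of its planned power. The simulations do not support that: crude power for the primary endpoint was 81% to 84%. What is forgone is power beyond the plan.

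Fourth, large hospital variation may be unrealistic. A logit SD of 0.8 around 57.5% puts hospitals one SD either side at about 38% and 75% tumour free margins. One reference pathologist examines all specimens (Outcome parameters), which removes one source of such variation. This is fair, and it is why the small-variation rows matter as much as the large ones.

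Finally, modelling the scoring physician needs the physician's identity. The article says that physicians score difficulty, not that their identity is recorded with the score.

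**Conclusion.** The point holds as an efficiency and coherence issue. It rests mainly on two things the article fixes: an unadjusted t test for outcomes randomised within hospital, and an adjustment rule that would not bring hospital in.

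For the t-tested outcomes, type I error is about 4.5% to 3%, with roughly 1 to 4 points of power forgone, at an assumed ICC of 0.05 to 0.20. Specimen weight is unaffected in practice on the protocol's own 10 g and 3 g. For the primary endpoint the loss is conditional on an unstratified interval: under 1 point up to logit SD 0.5 and about 2 to 4 points for large variation, with the planned 80% still met.

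The six hospitals, their equal or near-equal sizes, the between-hospital variation and the control rates are all assumptions; the article states none of them.

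**What to change.** State in the Statistical analysis section or the analysis plan that hospital enters the analyses regardless of observed baseline balance:

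- **Specimen weight and size, difficulty, discomfort:** replace the t test with a linear model containing arm and hospital.
- **Tumour free margins:** report the risk difference with a 95% confidence interval stratified by hospital, for example Mantel-Haenszel, with small hospitals pooled by a rule set beforehand.
- **Difficulty scores:** add a physician effect only if the scoring physician is recorded.

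The cost is wording. Hospital is already known for every patient because it is the randomisation stratum, and sample size and trial conduct do not change.
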